### Study setting

2.1

This is a multicentre, prospective, uncontrolled interventional trial with repeated pre- and per-stimulation measurements. The population of interest is patients suffering from SE-AN. After enrolment, patients will perform a complete preoperative workup, including metabolic assessment, neurocognitive evaluation, including emotional processing to specific AN stimulus, brain MRI. A DBS system will be implanted during surgery under general anesthesia. A 24-month follow-up will allow to observe and manage, if necessary, possible DBS-related complications and to perform two postoperative workups. DBS parameters will be optimized during this 24-month follow-up.

The sponsor of this study is the GHU Paris Psychiatry and Neurosciences, an academic hospital located in the fourteenth district of Paris (France). It is responsible for monitoring the study. It received a grant from the French Ministry of Health via the Programme Hospitalier de Recherche Clinique Interrégional 2019 (AOR19101-[name]). No company is involved in funding this study.

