#### Sample size

2.8.1

This is a pilot study and is not intended to evaluate the device’s effectiveness. The required number of participants was set at 12, following the Julious’s recommendations (64). Considering that seven patients out of sixteen presented serious adverse event(s) in one of the largest reported series to date, 12 patients should be enough to detect this effect size (28, 65).

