#### Statistical analysis

2.8.2

Statistical analysis will be performed at the end of the follow-up of all patients. The statistical analysis will be made in the biometrics center of the GHU Paris Psychiatry and Neurosciences. Data will be analyzed using JMP software (Version 14.1.0; SAS Institute Inc, Cary, North Carolina, USA). All analyses will be realized with a two-sided type I error rate of 5%. Quantitative data will be described by means and medians, standard deviations and interquartile ranges. Nominal data will be depicted by percentages with two-sided 95% confidence intervals. Time-to-event (time-to-relapse) data will be plotted by the Kaplan-Meier method. The proportions of missing data will be calculated. Patient characteristics (eligibility criteria, demographics, history, data at inclusion) will be described and compared by center. Quantitative data will be compared using Student’s t-test for a single sample (paired t-test) or ANOVA for repeated measures or non-parametric tests (Wilcoxon in paired series) when the distribution remains skewed even after appropriate transformation (Tukey power scale). Categorical data (pre vs. post) will be compared using Chi-2 or Fisher’s exact tests and or McNemar’s test for repeated measures.

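### For pre-versus-post categorical data the plan lists chi-square and Fisher's exact tests beside McNemar's test, although all such data are paired and only the paired test is valid

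*Protocol article*

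**What the plan says.** The protocol article, section 2.8.2 (Statistical analysis), gives one sentence on categorical outcomes: "Categorical data (pre vs. post) will be compared using Chi-2 or Fisher’s exact tests and or McNemar’s test for repeated measures". No rule says which of the three tests applies to which comparison. The same section plans to compare patient characteristics by center, which is an unpaired comparison, but the sentence on categorical tests does not refer to it. The label in brackets in "Categorical data (pre vs. post) will be compared using Chi-2 or" ties the tests to before-and-after data.

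The design makes those data paired. Section 2.1 describes an "uncontrolled interventional trial with repeated pre- and per-stimulation measurements", and section 2.8.1 states that "The required number of participants was set at 12". Section 2.5 adds that the preoperative assessment is repeated at 3, 12 and 23 months after surgery, which makes four occasions per patient.

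For quantitative outcomes, section 2.8.2 lists a "paired t-test) or ANOVA for repeated measures or non-parametric tests (Wilcoxon in paired series". On missing data it says "The proportions of missing data will be calculated". The significance level is common to everything: "All analyses will be realized with a two-sided type I error rate of 5"%.

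**The concern.** Chi-square and Fisher's exact test compare independent groups. Applied to 12 patients before and the same 12 after, they act as if there were 24 people and ignore which patients changed. Applied to the cross-table of pre by post status, they answer another question: whether status before predicts status after. Neither use tests change within patients.

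With three tests joined by or and and/or, the analyst may pick any of them after seeing the data. At 12 patients the listed tests can fall on different sides of 5%. Sections 2.8.2 and 3 leave no doubt that results will be tested and carried forward: the abstract and the discussion both say the trial should supply an effect size for later studies.

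A smaller matter concerns the quantitative scores. Classical repeated-measures ANOVA assumes sphericity and cannot use a patient with a missed visit. The listed non-parametric fallback, the paired Wilcoxon test, handles only two of the four occasions at a time.

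**Working it through.** The plan gives no p-value, power or sample size that depends on this sentence, so there is no stated figure to reproduce. The check sizes the effect of choosing one listed test over another.

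**Inputs.** From the protocol: 12 patients, two-sided 5%. Assumed: the pre and post proportions and the within-patient correlation (phi).

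**1. A single table, positive correlation.** Suppose 8/12 are positive before and 3/12 after, with 5 changing to negative and none to positive. Then 3 stay positive and 4 stay negative, and phi = (3×4 − 5×0)/√(8×4×3×9) = 12/29.4 = 0.41.

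- Chi-square, as two groups of 12: 24×(8×9 − 4×3)²/(12×12×11×13) = 86,400/20,592 = 4.20, p = 0.041.
- Fisher, as two groups of 12: p = 0.100.
- Exact McNemar: 2×(1/2)⁵ = 0.063.
- Asymptotic McNemar: (5 − 0)²/5 = 5.0, p = 0.025.

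Two results are below 0.05 and two above, so the conclusion depends on the test picked. The two forms of McNemar also disagree, so the form must be fixed as well.

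**2. The cross-table use.** Suppose 6 patients stay positive, 6 stay negative and nobody changes. Fisher on the pre-by-post table gives 2/C(12,6) = 2/924 = 0.002. McNemar has no discordant pair, so its exact p is 1. A highly significant result appears although no patient changed.

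**3. Behaviour over all tables.** All paired tables with 12 pairs were enumerated, with true pre and post proportions both 50%. Rejection rates at nominal 5%:

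| phi | chi-square | Fisher | asymptotic McNemar | exact McNemar |
|---|---|---|---|---|
| 0 | 6.4% | 2.3% | 4.8% | 1.4% |
| 0.3 | 2.7% | 0.7% | 4.9% | 0.5% |
| 0.6 | 0.4% | 0.06% | 2.1% | 0.05% |

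As positive correlation grows, chi-square becomes conservative, because it ignores the pairing that reduces the variance of the difference. For a true fall from 80% to 30% at phi 0.3, power is 80.4% for chi-square against 89.6% for asymptotic McNemar, and 61.8% for Fisher against 60.3% for exact McNemar. Exact McNemar is itself conservative at this size. It is preferred because it tests the right hypothesis with a guaranteed level, not because it gains power.

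**4. Repeated-measures ANOVA.** If patients with any missed postoperative visit could not be used, and a share m were missing at each of three visits independently (assumption), the expected number usable is 12×(1 − m)³: 12×0.95³ = 10.3, 12×0.90³ = 8.7 and 12×0.80³ = 6.1. The protocol gives no missing rate, so this is a range and not a forecast.

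**The case against.** The strongest reply is that the correct test stands in the same sentence, attached to repeated measures, so a competent analyst would use McNemar for pre/post data and keep chi-square or Fisher for comparisons by center. A reader might infer from the sentence that wrong p-values are planned. The text does not support that: it permits the invalid test and does not prescribe it. But the bracketed label attaches all three tests to pre/post data, so the permission is real.

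A reader might also infer that the unpaired tests mainly create false positives. The enumeration does not bear this out, since with positive correlation they are mostly conservative. Nor does every table flip. For 9/12 to 3/12 with 6 against 0 discordant (phi = (3×3 − 6×0)/27 = 0.33), chi-square gives 0.014, Fisher 0.039 and exact McNemar 0.031, all below 0.05. With the same margins and 7 against 1, exact McNemar gives 18/256 = 0.070, but phi is then (2×2 − 7×1)/27 = −0.11, an unlikely sign for repeated measures.

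Little rests on the sentence. The efficacy endpoints in section 2.4.2.1 are essentially quantitative, the acceptability percentages in section 2.4.2.1.1 have no preoperative counterpart, and the primary endpoint in section 2.4.1 is monitored by a separate sequential binomial test. This stands, and it limits the importance of the point.

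On the scores, it is tempting to read the plan as discarding patients with incomplete data. It states no complete-case rule, and handling of missing values may sit in an analysis plan that is not shown. All three listed methods for quantitative data respect the pairing.

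**Conclusion.** The categorical part holds. Chi-square and Fisher's exact test are stated for a comparison that is always paired in this trial, and the and/or leaves the choice open. The size is modest: single tables can fall on either side of 5% (0.041 against 0.063 in the worked case), while on average, with positive within-patient correlation, chi-square loses power and does not inflate error. These figures rest on assumed proportions and correlations with 12 complete pairs. The consequence is confined to secondary analyses of a pilot that section 2.8.1 says is not meant to evaluate effectiveness.

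The point on repeated-measures ANOVA is only a suggested improvement. Any loss of patients would be a property of the classical method, and its extent depends on a missing rate that the protocol does not give.

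**What to change.** Replace the sentence on categorical data. For pre/post comparisons, use the exact McNemar test and report the paired difference in proportions with its 95% CI. Reserve chi-square or Fisher's exact test for unpaired comparisons, such as those by center. With 12 patients the interval should lead the reporting and the p-value should support it.

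As a secondary change, for scores taken on four occasions replace classical repeated-measures ANOVA by a linear mixed model: visit as a fixed effect, patient as a random effect, REML estimation with small-sample degrees of freedom, and all available visits of all operated patients. Report change from the preoperative visit with 95% CI.

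Both are changes to analysis wording. They need no new data, visits or patients, and only slightly more analysis work for the mixed model.

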### Ethics and dissemination

2.9

The study protocol was approved by the Comite de Protection des Personnes (CPP) Est-II (n°: 21.05.12.69252) and by the ANSM (French National Agency for Medicines and Health Products Safety). Investigators will ask all participants to give written informed consent before participation, and all data will be recorded anonymously. The study will be conducted according to ethics recommendations from the Helsinki Declaration (World Medical Association, 2013).

The need to repeatedly inform patients and ensure their understanding of the implications of this protocol was taken into consideration when drafting this protocol (66–68). Several measures have been taken to guarantee fair, clear, and appropriate information: 1) patient cases are systematically discussed during multidisciplinary meetings; 2) patients are only referred by physicians who have been treating them for years (referring physicians); 3) delays of several weeks are always respected between each step of the protocol, 4) the implication of a caregiver is mandatory for inclusion. An Independent Monitoring Committee (IMC) checks patient recruitment and the continuation in the study. The first meeting of the IMC has to be done before the first inclusion and then the IMC meets at least twice annually to discuss possible safety issues. The four members of the IMC are independent of sponsor, laboratory, and investigator. The members of the IMC are: one biostatistician with expertise in clinical research; two neurosurgeons with expertise in functional neurosurgery and DBS; one psychiatrist with expertise in the management of SE-AN. The existence of psychiatric emergencies within the GHU Paris Psychiatry and Neuroscience hospital and the long history of links between psychiatry and neurology guarantee high standards in terms of research ethics (69, 70).

All data collected during this trial are the property of the research sponsor, the GHU Paris Psychiatry and Neuroscience, and may not be communicated to a third party under any circumstances without the written consent of the sponsor. At the end of the research, the participant has the right to be informed of the research’s overall results, according to the modalities that will be specified during the inclusion interview. Participants will have the possibility of communicating their e-mail addresses to the investigator who collected their consent to obtain the overall results of this research when they become available.

The results will be published after final analysis in scientific articles in peer-reviewed journals and may be presented at national and international conferences. Any publication or communication (oral or written) is decided by mutual agreement between the investigators and the sponsor. Individuals who contribute to the production of the publication will be granted authorship.

## Discussion

3

Patients suffering from treatment-resistant AN have limited treatment options nowadays. They exhibit poor outcomes, even in expert centers (71). Our study protocol aims to support the growing literature on DBS for treatment-resistant AN.

Costs associated with AN are mostly related to hospital stays (72). The average length of stay for patients with AN is higher than 100 days in Europe (73). During hospitalization in expert centers, refeeding approaches lead to a clinical remission according to the BMI, even with higher-calory refeeding (74). However, relapse of AN arises frequently during the 18 months after hospitalization (75). This underlines the need to manage more community-oriented therapeutic approaches in AN patients. Our study does not require very low BMI to include the patient: the aim is more to manage the deinstitutionalization of AN patients than to obtain weight gain.

Whereas the safety of DBS is now well-established in neurological conditions, this question remains for treatment-resistant AN patients (76, 77). This study will help to refine the expected complication rate in front of these malnourished patients. Moreover, DBS is reversible and customizable. These two points explain why DBS, a reversible neuromodulation technique, should always be considered rather than irreversible lesion techniques (such as thermolesions, radiosurgery) in psychiatric patients.

The main limitations of this study are the single arm and open-label characteristics. This study design has been considered as mandatory by the French authorities. After confirmation of the DBS safety in patients with treatment-resistant AN, a larger study will be possible. The small study sample is in line with the main outcome of safety. We have decided to monitor the patient’s quality of life with two scales translated and validated in French, to minimize the common misgrading of quality of life in anorexia nervosa patients (78). However, these scales are generic and an eating disorder-specific measure would represent a nice to further studies (79). The measurement of healthcare intervention acceptability should investigate multiple aspects: despite numerous psychiatric follow-up visits, only limited data will be collected during the protocol (62). The development of a specific theory-informed questionnaire about DBS for SE-AN would have been a significant improvement and should be done for the next studies (80, 81).

The strengths of this study are the use of a directional DBS system, the target chosen for AN purpose only, and the patient inclusion not during a severe relapse of their treatment-resistant AN. This will help to obtain the real effect size of NAc DBS for treatment-resistant AN.
